**13. Ethical considerations**

**13.1 Adverse events and benefits**

**13.1.1 Potential adverse events**

Participants may feel embarrassed or anxious when we collect some privacy information. Participants may fear of privacy disclosure when we deliver interventions using SMS or WeChat. We will deliver interventions during non-work hours and adapt it based on participants’ requirement. We will capture potential adverse events via spontaneous self-report. Participants can contact us through phone or WeChat to report adverse events. If any participant feel they have experienced an adverse event from participating in this trial, they can withdraw at any time.

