**Figure S1. Model framework of differentiated digital intervention**

**5. Overview of design**

This study will be a pragmatic RCT with two parallel arms designed for MSM living with HIV currently on ART. Participants will be randomly assigned in a 1:1 ratio to the intervention arm or the control arm, stratified by different digital strategies. For each stratum, block randomization will be triggered once four participants are recruited. Participants in the intervention arm will receive 6-month comprehensive interventions including ART medication messages, medication reminders, peer education and online group discussion. Participants in the control arm will receive messages on health behavior and nutrition. The study will last about 7.5 months. The first 1.5 months include the recruitment period and the baseline survey. Two follow-up surveys will be administrated every 3 months.

The flowchart of this differentiated digital intervention trial is displayed in Figure S2. The SPIRIT figure of study timeline is displayed in Figure S3.

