**11. Data collection**

Data will be collected using written questionnaires. At baseline, we will collect information about socio-demographic characteristics (including age, household, education, occupation, monthly income and marital status, etc), behavioral characteristics (including homosexual behaviors, sexual orientation disclosure, HIV status disclosure), HIV clinical knowledge, basic information of ART (including time and frequency of daily medication-taking, frequency of missed doses in the month, reasons of missed doses, side effects, etc), HIV treatment adherence self-efficacy, ART medication knowledge and quality of life. In follow-ups, we will collect information about ART adherence within the past month, HIV clinical knowledge, ART medication knowledge, HIV treatment adherence self-efficacy and quality of life through self-administered questionnaire. Besides, we will collect CD4 T-cell counts and HIV detectable viral load from medical records in the hospital.

A verification mechanism has been adopted to improve data quality. When a questionnaire is completed, investigators will check immediately to identify logical errors or missing data to verify with the participants. Participants will be reimbursed after the verification is completed.

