**13.3 Monitoring**

An external data monitoring committee will not be formed for this study because the potential harm to participants is minimal. But we will establish an internal expert advisory committee (including university professors, clinical practitioners, CDC staff, and leaders of MSM organization) to guide protocol formation, data collection, data management, and data analysis. Regular meetings will be established to review trial progress. All participants are informed that they can withdraw at any time and they are provided a phone number or WeChat account to contact the primary investigator (PI) with any questions or concerns.

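### Adverse events are captured only if a participant volunteers them, although both arms complete two follow-up questionnaires that list no harm item: under-counting is likely, and unequal capture between arms is possible but not shown

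*Protocol*

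**What the plan says.** Section 13.1.1 foresees two harms. One arises from the surveys: "Participants may feel embarrassed or anxious when we collect some privacy information". The other arises from delivery: "Participants may fear of privacy disclosure when we deliver interventions using SMS or WeChat". It then fixes how harms are found: "We will capture potential adverse events via spontaneous self-report". The route is "Participants can contact us through phone or WeChat to report adverse events", worded the same for both arms.

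Section 5 sets the survey schedule: "Two follow-up surveys will be administrated every 3 months". Section 11 lists what those surveys contain: "In follow-ups, we will collect information about ART adherence within the past month, HIV clinical knowledge, ART medication knowledge". The list then adds self-efficacy and quality of life. No harm or privacy item is listed. Side effects appear only in the baseline list, among the basic ART information.

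Under section 7, participants are not masked to how they receive the service and providers know the assignment, but field surveys are run by blinded team members. Section 13.3 dispenses with an external monitoring committee "because the potential harm to participants is minimal".

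**The concern.** Unprompted reporting finds only what a participant recognises as a harm, thinks worth mentioning and is willing to raise. That suits the harm foreseen here badly. A man uneasy about what arrives on his phone is asked to use the phone, or WeChat, to say so. A man embarrassed by the questions must bring up his embarrassment himself.

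The protocol already has a better opportunity. Every participant is due to be surveyed twice after allocation, and under section 11 each form is checked with him on completion. A question put there would reach all surveyed men in both arms in the same way.

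What is at stake is how a short adverse-event list will be read. Section 13.1.2 looks ahead to integrating the intervention into the management of people living with HIV and to its use in other countries. Someone deciding on that could take a near-empty list as evidence of safety, when it may mean only that nobody was asked.

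**Working it through.** The protocol states no harm rate, reporting rate or safety power, so there is no figure of its own to reproduce. The check is a reading of the sections, followed by an illustration.

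**1. Is capture unprompted only?** Section 13.1.1 gives one method and one participant-initiated route. Section 13.3 adds a phone number or WeChat account for questions or concerns, which also depends on the participant. Section 11 lists adherence, two knowledge measures, self-efficacy and quality of life at follow-up. Quality of life is a secondary outcome (section 9.2). It may register distress, but it does not ask whether the study caused it. So no solicited collection of harms is described.

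**2. Does scheduled contact differ between arms?**
- Intervention (sections 8 to 8.3): 12 medication messages, 6 clinical messages and about 6 peer items (every two weeks from month 3; section 8.2 gives six videos). 12 + 6 + 6 = 24. Daily reminders are optional. One stratum also has a QQ group that includes a team member and a physician.
- Control (section 8.4): 12 items every two weeks. The sentence can also be read as 12 behavioural items plus an unnumbered set of nutrition messages, so 12 may be too low.

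Contact therefore differs, at about 24 against 12 on the first reading of section 8.4.

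**3. What could this do to the counts?** With 570 men allocated 1:1, each arm has 570 / 2 = 285.

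Expected recorded events = 285 × true risk × probability that an event is volunteered.

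Both the risks and the reporting probabilities below are assumptions. True risk is set equal in the two arms.

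| True risk | Events per arm | Volunteered, control / intervention | Recorded, control | Recorded, intervention | Apparent ratio, intervention to control |
|---|---|---|---|---|---|
| 2% | 5.7 | 30% / 30% | 1.71 | 1.71 | 1.0 |
| 2% | 5.7 | 20% / 40% | 1.14 | 2.28 | 2.0 |
| 2% | 5.7 | 40% / 20% | 2.28 | 1.14 | 0.5 |
| 5% | 14.25 | 30% / 30% | 4.28 | 4.28 | 1.0 |
| 5% | 14.25 | 20% / 40% | 2.85 | 5.70 | 2.0 |
| 5% | 14.25 | 40% / 20% | 5.70 | 2.85 | 0.5 |
| 10% | 28.5 | 30% / 30% | 8.55 | 8.55 | 1.0 |
| 10% | 28.5 | 20% / 40% | 5.70 | 11.40 | 2.0 |
| 10% | 28.5 | 40% / 20% | 11.40 | 5.70 | 0.5 |

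Under-counting follows from any reporting probability below 1. The apparent ratio is simply the ratio of the two reporting probabilities, about which the protocol says nothing.

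**The case against.** The strongest reply is that this is a low-risk messaging trial, that unprompted capture is a deliberate and stated choice, and that nothing in it is contradictory or miscalculated. The protocol also reduces the risk at source. Reminders omit the words HIV and AIDS, delivery is outside working hours and adapted on request, entry to the QQ group is controlled, and contact details sit on a password-protected phone. Section 11 may only summarise the questionnaire. All of this stands, and it is why the point is minor. It does not change the fact that no question about harms is described.

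A reader might go further and infer that reports will be unequal between arms, with more from the intervention arm because it hears from the team more often. The protocol does not support that. The reporting route is the same in both arms, and stratification by digital strategy balances the channel. The scheduled items are mostly outgoing content, and receiving a message is not being asked about harm. More messages could also mean more real exposure, in which case a difference would be genuine.

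A reader might also infer that arm counts are needed to justify the absence of an external committee. Section 13.3 makes an advance judgement that does not rest on those counts, and no comparison of harms between arms is planned. Finally, section 13.1.1 names fear of disclosure, which should not be counted as if it were disclosure itself.

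**Conclusion.** The point holds as a modest weakness in how harms are ascertained. Capture depends wholly on the participant coming forward, and the two follow-up questionnaires as listed do not ask. Under-counting is likely. This rests on the assumption that not every affected man will volunteer a report, which is reasonable when the foreseen harms are embarrassment and fear of disclosure.

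Different capture between arms is a possibility, given the difference in scheduled contact and the lack of masking. It is not a demonstrated bias. Neither its size nor its direction can be derived from the protocol, and the table shows only that equal, higher or lower intervention counts could all arise from the same true risk. The primary outcome, the sample size and the efficacy analysis are untouched.

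**What to change.** Add one fixed item to the month-3 and month-6 questionnaires, identical in both arms. For example, ask whether anything received from the study led to unwanted disclosure, distress or another problem, with space to describe it. Report the answers by arm with the number asked as denominator. Keep volunteered reports as a separate supplement, because a man who withdraws after an event may never reach the next survey. At the planned 20% loss, the item would reach about 285 × 0.8 = 228 men per arm.

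The item should not name reminders or the group. These belong to the intervention only, and an answer mentioning them could reveal allocation to the blinded staff who check each form while collecting a self-reported primary outcome. Neutral wording limits this risk but does not remove it, since a free-text answer may still give the arm away.

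The cost is one question on two existing forms, one table and a few more minor events to record. No extra visits or staff are needed. If the month-3 survey has already been run, the item can still go on the month-6 form.

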**13.1.2 Benefits of this study**

The comprehensive intervention of this study may promote participants to obtain health messages about ART, develop good habits of taking medications on time, get psychological and social support, and eventually improve ART adherence and quality of life. In addition, some participants may receive financial incentives by participating in our online clock-punching activities.

This study will provide reference for digital intervention (especially for Internet-based digital intervention) on ART adherence in Chinese contexts. Once proven effective, this intervention can be integrated into PLWH management and further considered in LMICs where there are large numbers of PLWH who can access text messaging or instant messaging services.

**13.2 Protocol amendments**

If any protocol amendments are needed over the course of the trial, these changes will be reported to relevant parties by email. Results of this trial will be distributed to national stakeholders.

**13.3 Monitoring**

An external data monitoring committee will not be formed for this study because the potential harm to participants is minimal. But we will establish an internal expert advisory committee (including university professors, clinical practitioners, CDC staff, and leaders of MSM organization) to guide protocol formation, data collection, data management, and data analysis. Regular meetings will be established to review trial progress. All participants are informed that they can withdraw at any time and they are provided a phone number or WeChat account to contact the primary investigator (PI) with any questions or concerns.

**13.4 Compliance**

[name] and [name] will lead the development and implementation of the differentiated digital intervention and overall study coordination. [name] will be responsible for fiscal administration. The PIs will communicate regularly by phone or email to discuss study design, trial progress, and potential problems.

**13.5 Confidentiality**

All written questionnaires and informed consents were stored in locked, fireproof file cabinets. Meanwhile, all survey questionnaires will be entered into a secure computer with passwords and firewalls. This computer will be used for saving survey data. A smartphone with passwords will be used to save participants’ personal information (including phone number, WeChat account and QQ account) and deliver digital interventions for all participants. Only a PI and a designated health provider from the study site will have the password to access the smartphone.

**13.6 Ethical approval**

This study was reviewed and approved by the Ethical Review Committee of School of Public Health in Shandong University (20190210).

**13.7 Informed consent**

Before participating the baseline survey, all participants will be presented with a written informed consent. Once participants provide written consent (pseudonymous is allowed), they are required to complete study questionnaire.

